### Data collection

Assessment of all variables will occur at baseline, 6 months, 18 months, and 30 months which correspond with the study phases. Women will be asked to attend a short assessment session at 3 months, 12 months, and 24 months which will include all measures except the Health Promotion Model cognitive-perceptual variables, blood glucose and lipids, self-reported diet, accelerometer data and estimated cardiorepiratory fitness via the 400-meter walk test. Established reliable and valid measures will be used for all assessments.

Questions pertaining to general demographic information and health history will be asked. The Patient-Reported Outcomes Measurement System (PROMIS-29 Profile v1.0) will be administered to obtain subscales of physical function, anxiety, depression, fatigue, sleep disturbance, social role, pain interference and intensity [49].

#### Blood pressure and resting heart rate

Resting heart rate (using the radial pulse for 60 seconds) and blood pressure will be measured following 5 minutes of quiet sitting following standardized methods [50]. At each visit, at least two blood pressure measurements separated by at least 30 seconds will be obtained. Systolic blood pressure is the appearance of the first Korotokoff sound. Diastolic blood pressure is the disappearance of Korotokoff sounds. Both systolic and diastolic blood pressure will be recorded as the mean of the two measurements that were within 5 mmHg. Participants will be asked to avoid caffeine, exercise and smoking for at least 30 minutes prior to an assessment.

#### Eating

The Web version of the 1998 Block Health Habit and History Questionnaire will be used to measure the usual self-selected diets of individuals over a period of time [51]. This survey asks for the frequency of consumption of particular food items consumed in the last 3 months. It provides information about daily caloric intake, % of dietary intake by categories (protein, carbohydrate, % fat, % saturated fat), intake of daily servings (fruits, vegetables, whole grain, low fat dairy) and daily mineral consumption.

#### Physical activity

The Behavioral Risk Factor Surveillance System (BRFSS): Physical Activity Module consisting of a 7-item self-report instrument will be used to determine the women's participation in moderate or vigorous activity by days per week and minutes per day [52]. In addition, the BRFSS allows for categorization of participation by physical activity as recommended, insufficient or inactive as defined by the United States Department of Health and Human Services [53]. Using a format similar to the BRFSS, two items from the Women's Exercise Injuries: Incident and Risk Factors study will be added to capture self-reported minutes per day and days per week spent in strengthening activity and walking [54].

Time spent weekly at each study phase (baseline, 6-month, 18 month and 30-month) in light, moderate and vigorous intensity physical activity will be measured objectively by the triaxial Actigraph accelerometer (GT3X) using methods consistent with the publicly available SAS code developed to process the 2003-2004 NHANES accelerometer-determined physical activity data [55,56]. Individuals will be asked to wear the Actigraph for 24 hours a day, except when showering, and to record the time spent during sleeping for comparison to the Actigraph data.

The 400-meter walk test, shown to have excellent reproducibility and strong associations with estimated and measured maximum oxygen consumption in midlife and older women, will be used to provide an estimate of cardiorespiratory fitness [57]. Women will be asked to walk a 400-meter course at a brisk pace with total walk time recorded, and heart rate recorded in beats per minute recorded prior to and immediately following the walk. To minimize learning effects at baseline, the best walk times of two trials completed on separate days will be recorded. Lower body strength will be assessed using the 10-repetition timed chair stand test that requires completion of 10 full stands from a sitting position as quickly as possible while timed in seconds [58]. Upper body strength will be measured using the timed arm curl test which involves counting the number of times a woman can curl a 5-pound hand weight through a full range of motion in 30 seconds [59].

#### Biomarkers affected by activity and eating

The Tanita Model [TBF-215, Tanita Corporation of America, Inc., [name]] will be used to measure height, weight and percent body fat following the manufacturer's instructions. Women will be asked to fast within 4 hours of the test, not exercise intensively within 12 hours of the test, avoid alcohol 48 hours before testing and to void the bladder within 30 minutes prior to the test, as this bioelectrical impedance analysis system measure is sensitive to hydration status [60,61].

BMI will be calculated as weight in kilograms divided by height in meters-squared [26]. Waist circumference will be measured by placing a tape in a horizontal plane around the abdomen at the level of the iliac crest at the end of expiration. Hip circumference will be measured by placing a tape in a horizontal plane at the widest element of the hips between the greater trochanters and the gluteal fold. These anthropometric procedures will require a snug tape that is parallel to the floor but is held without skin compression with the average of two trials recorded [26].

Blood specimens will be drawn after a 12-hour fast to determine total cholesterol, low-density lipoprotein (LCL-C), high-density lipoprotein (HDL-C), triglycerides and fasting glucose following standardized protocols.

#### Measurement of behavioral determinants

Women will complete validated surveys to assess their perceptions of benefits and barriers, interpersonal support and self-efficacy for healthy eating and activity. The instruments will include the Exercise Benefits/Barriers Scales [62]; Healthy Eating Benefits/Barriers Scales [44]; Self-efficacy for Eating Habits Scale; Self-Efficacy for Exercise Habits Scale [63]; and Family Support for Exercise Habits Scale and Friend Support for Exercise Habits Scale; and Family Support for Healthy Eating Habits Scale and Friend Support for Healthy Eating Habits Scale [64].

#### Process evaluation

Process evaluation forms without identifiers, but color-coded for group designation, will be mailed to participants with a postage paid envelope for return at 6, 18, and 30 months to determine the degree to which the program was implemented as planned. Questions are designed to assess the women's recall of the intervention, the extent to which they participated and how helpful the intervention was in assisting them to make change. Website use will be collected from server log files. In addition, at 6 and 18 months, we will conduct telephone interviews with a random sample of approximately 10 participants from each intervention group, seeking representation from those women who were successful with weight loss of at least 5% and those who have not been successful with this weight loss. A similar approach will be followed at the end of the study, 30 months after baseline, using a face-to-face focus group format for each of the intervention groups to be conducted at the rural assessment site.

#### Data analysis

The primary analysis will focus on each phase separately, testing planned pairwise comparisons of the intervention groups over time using generalized estimating equations (GEE). The primary end point will be average change in outcome from the beginning of each phase. GEE also will be used to test whether the groups differ over time in the proportion of women meeting 5% and 10% weight loss goals. Secondary analyses will include a trend analysis of differences in the pattern of change across the entire 30 months of the study. All primary analyses will be consistent with the intent-to-treat principle and imputation of missing values may be undertaken, depending upon the extent and pattern of missing data.

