### Sample size

Sample size needed for the study was estimated for a test of group difference in response averaged across time using generalized estimating equations [41]. Calculations assumed a group mean difference of .45 standard deviations based on median values on these outcomes in [12,15] and our pilot work, two measurement times per phase, within-subject correlation ≤ .5, and α of .017 (Bonferroni adjustment for three pairwise comparisons). For the most conservative pairwise test that will be conducted, the two-sided comparison of the groups receiving counseling, 76 participants will be needed in each group. A total sample size of 306 will be recruited to allow for attrition of 25%, consistent with that experienced in both published weight loss studies and our own pilot work.

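### The phase 1 GEE on average change should state adjustment for the month-0 value of each continuous outcome; the gain is real but does not carry over to phases 2 and 3

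*Protocol article*

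**What the plan says.** The Data analysis section takes the three phases one at a time, "testing planned pairwise comparisons of the intervention groups over time using generalized estimating equations (GEE". It then defines what is compared: "The primary end point will be average change in outcome from the beginning of each phase". Neither sentence mentions a baseline term, either as included or as left out. Phase 1 begins at the pre-randomization baseline. Phases 2 and 3 begin at months 6 and 18, after randomization.

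The Sample size section plans for a time-averaged group difference in response by GEE. "Calculations assumed a group mean difference of .45 standard deviations", with "two measurement times per phase, within-subject correlation ≤ .5" and a two-sided alpha of .017. It takes no credit for baseline adjustment. The Data collection section shows that not every outcome has two follow-ups per phase: lipids, glucose, self-reported diet, accelerometer data and the 400-meter walk are omitted at months 3, 12 and 24.

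**The concern.** A raw change score subtracts the whole starting value, whatever the strength of its relation to follow-up. Unless that relation is very strong, this carries baseline noise into the comparison. A model with the starting value as a covariate lets the data set the weight. It is never less precise in large samples and also removes chance baseline imbalance.

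If the model is fitted as the article describes it, with no covariate, precision is given up in the phase 1 comparisons. The loss is largest where a woman's repeated values correlate only modestly. The documents give no outcome-specific correlations, but eating, activity and some biomarker outcomes are the likely candidates, and the Study design section lists these among the primary outcomes.

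**Working it through.** **Inputs from the Sample size section.** Difference .45 SD; two measurements per phase; correlation at most .5; two-sided alpha .017 (z = 2.387); 76 per group; 25% attrition; 306 in total. Power is not stated, so 80% (z = .842) is assumed.

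**1. The plan's own figure.** The mean of two measurements with correlation .5 has variance (1 + .5)/2 = .75 in SD² units. Then n = 2 × .75 × (2.387 + .842)² / .45² = 77.2, or 78 per group, against 76 stated. Power at n = 76 is 79.3%. For attrition, 76/.75 = 101.3, so 102 per group, and 3 × 102 = 306. The sample size reproduces to within two women per group without any baseline adjustment.

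**2. Phase 1, two follow-ups, exchangeable correlation r.**
- Mean change: (1+r)/2 + 1 − 2r = 1.5(1−r).
- Adjusted for month 0: (1+r)/2 − r² = (1−r)(1+2r)/2.
- Ratio, adjusted to change: (1+2r)/3.

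| r | change | adjusted | cut |
|---|---|---|---|
| .3 | 1.05 | .56 | 46.7% |
| .5 | .75 | .50 | 33.3% |
| .8 | .30 | .26 | 13.3% |
| .9 | .15 | .14 | 6.7% |
| .95 | .075 | .0725 | 3.3% |

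All values of r here are assumed; .5 is the plan's ceiling.

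Power at n = 76 is Φ(.45/√(2f/76) − 2.387), where f is the variance. At r = .5 it rises from 79.3% (f = .75) to 93.8% (f = .50), and n for 80% power falls from 78 to 52. For weight, take r = .9-.95 and read .45 in units of the SD of change. Then n falls only from 78 to 73-75, and power at 76 rises from 79.3% to 81-82%.

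**3. Phase 1, one follow-up.** Change: 2(1−r). Adjusted: 1 − r². Ratio: (1+r)/2. At r = .5 this is 1.00 against .75, a 25% cut. It applies to diet, lipids, glucose, accelerometer and the 400-meter walk.

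**4. Phases 2 and 3.** Phase 2 change is the mean of months 12 and 18 minus month 6.
- *Adjusting for month 0.* The covariance of this change with month 0 is (r + r)/2 − r = 0, so the variance stays at .75 when r = .5. Phase 3 behaves the same way. If correlation instead decays with time (assumed .5 or .9 per six months), the cut in phase 2 is modest: 1.00 to .902, or .240 to .223.
- *Adjusting for month 6.* The variance falls from .75 to .50 at r = .5, but the covariate is itself an outcome of treatment. Suppose the arms differ by .45 SD at month 6 and change equally afterwards. The change analysis then estimates 0, while the adjusted analysis estimates .45(1−r): .225 SD at r = .5, .045 SD at r = .9.

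**The case against.** The strongest objection is that the article is silent on covariates. It does not exclude a baseline term, a change end point is compatible with one, and a covariate list may sit in a full protocol or SAP that is not shown. A reader might infer that the plan rules adjustment out; the text does not support that. What stands is that the end point is set down as change and no adjustment is stated with it.

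A second stronger reading is that a third of the variance is lost throughout the trial. This fails on three counts. The one-third figure needs two follow-ups. It needs r = .5, whereas "within-subject correlation ≤ .5" is a ceiling and is not said to be the correlation between baseline and follow-up. And it is confined to phase 1, as step 4 shows.

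A third is that 76 per group is too few for a change analysis. If .45 is in SDs of the raw outcome and the baseline correlation is .3, power for raw change would be 63%, against 91% adjusted. But the article does not say which SD or which correlation it means. If both refer to change scores, two changes from a common baseline have covariance 1−r and variance 2(1−r). Their correlation is then .5 for any r, and the same .75 factor and n of about 78 follow. The stated sample size is therefore not shown to be wrong.

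Finally, baseline imbalance in phase 1 is chance and not bias, and the expected gain for weight, the subject of the primary aim, is small. Both points stand. They limit the size of the gain without removing it.

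**Conclusion.** The point holds for phase 1 only. Stating month-0 adjustment for each continuous outcome would improve precision at almost no cost. The variance cut is one third at r = .5 for outcomes measured twice in the phase, more if r is lower, and 25% at r = .5 for outcomes measured once. For weight it is about 3-7% if r is .9-.95. These figures rest on exchangeable correlation, equal variances over time and assumed values of r.

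Phases 2 and 3 need their own decision, since neither available covariate gives a free gain under the exchangeable model. The 76 per group and 306 in total stand without the adjustment. This is an efficiency improvement, not an error that invalidates the analysis.

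**What to change.** For phase 1, state that the GEE for each continuous outcome includes the month-0 value of that outcome as a covariate, allowing a baseline-by-time term, and that the adjusted group difference is the test. The data are already collected, and the cost is one covariate per model (about one degree of freedom, slightly more with the interaction).

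For phases 2 and 3, state whether the question is change within the phase or the cumulative difference since randomization, and which starting value, if any, enters the model and why. Modelling the follow-up level on month 0 answers the cumulative question; it is not a more precise version of within-phase change. If the phase-start value is used, say that it is post-randomization and how the estimate is to be read.

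It would also help to say whether the .45 SD and the correlation ceiling refer to response or to change. All of this takes a few sentences and no change to the sample size.

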## Discussion

Providing an effective intervention for behavior-change to promote weight loss and weight maintenance among midlife and older rural women is needed, as these women have a high prevalence of overweight and obesity. These theory-based web-delivery interventions offer innovative approaches to offer weight loss and maintenance counseling to this hard-to-reach vulnerable group of rural women.

The intervention has merit in investigating the effectiveness of distance delivery methods to encourage multiple behavior-changes in the areas of healthy eating and activity for weight loss. A strength of this study is that it examines a comprehensive approach for behavior-change by incorporating the Health Promotion Model's concepts of behavior-specific cognitions (barriers to and benefits of action, interpersonal support and self-efficacy for healthy eating and activity), self-monitoring (home weight scales, pedometers and logs), individualized feedback, and cues to action (goal setting) as part of the intervention. In addition, the study design provides an extended period for weight maintenance, which has been linked with continued weight maintenance in other populations.

Limitations are acknowledged as self-reported measures of activity and eating may be biased by social desirability of response, although self-reports will be validated by assessments of biomarkers known to change in conjunction with these behaviors. As it is not feasible to randomly sample women who are overweight or obese, the sample of convenience may limit the generalizability of the results although the sample will be representative of midlife and older rural underserved women and the women will be randomized to intervention group. The lack of minorities in the areas from which the women will be recruited will limit the generalizability of results to the general population. We anticipate that the sample is biased in favor of those who have a stronger interest in changing their health behaviors and of those who have Internet access. Increased societal attention towards addressing overweight and obesity that permeates the media may influence behavior-change concurrently with our intervention.

This research will implement a distance model for delivery of lifestyle modification and information to provide easily accessible lifestyle guidance to a hard-to-reach clientele. If effective, these interventions may also provide benefit to over-worked and under-reimbursed rural providers who may not have the time to deliver lifestyle modification programs. If any of the interventions are found effective, follow up testing for pre-packaged programs for the public offered through settings such as public health departments, primary care offices, or health education settings may be appropriate.
